## Abstract

**Background:**

Farmers are a vulnerable population for developing depression or other mental health disorders due to a variety of risk factors in their work context. Beyond face-to-face resources, preventive internet- and tele-based interventions could extend available treatment options to overcome barriers to care. The German Social Insurance Company for Agriculture, Forestry and Horticulture (SVLFG) implements several guided internet- and mobile-based interventions and personalised tele-based coaching for this specific target group provided by external companies within a nation-wide prevention project for their insured members. The current study aims to evaluate the implementation process and to identify determinants of successful implementation on various individual and organisational levels.

**Methods:**

The current study includes two groups of participants: 1) insured persons with an observable need for prevention services, and 2) staff-participants who are involved in the implementation process. The Reach, Effectiveness, Adoption, Implementation and Maintenance (RE-AIM) framework and the Consolidated Framework for Implementation Research (CFIR) will be used to track and evaluate the implementation process. A mixed-method approach will provide insights on individual and organizational level (e.g. degree of normalization, readiness for change) and helps to identify determinants of successful implementation. In-depth insights on experiences of the participants (e.g. acceptance, satisfaction, barriers and facilitating factors of intervention use) will be yielded through qualitative interviews. Focus groups with field workers provide insights into barriers and facilitators perceived during their consultations. Furthermore, intervention as well as implementation costs will be evaluated. According to the stepwise, national rollout, data collection will occur at baseline and continuously across 24 months.

**Discussion:**

The results will show to what extent the implementation of the internet- and tele-based services as a preventive offer will be accepted by the participants and involved employees and which critical implementation aspects will occur within the process. If the implementation of the internet- and tele-based services succeeds, these services may be feasible in the long-term.

**Trial registration:**

German Clinical Trial Registration: DRKS00017078. Registered on 18.04.2019.

## Background

Depressive disorder is a common condition with a 12-month prevalence rate of 8.56% in European countries [1]. Previous research has shown that farmers [2–5] and employees in related occupations (e.g. forestry and fishery workers) [6] are at an increased risk for developing mental health problems, especially depression, compared to non-agricultural occupations. Risk factors for mental disorders associated with agricultural jobs include: work-related stress [7, 8], longer work hours [3], poor harvest and weather [2], financial problems [9], health problems [8, 10] and exposition to pesticides [8].

At the same time, farmers mainly live in rural areas with limited mental health care. In Germany, the availability of on-site psychotherapy is additionally restricted by long waiting times in rural areas [11, 12]. Furthermore, stigma surrounding mental disorders and resistance to mental health care are reported in rural areas [5]. Especially male farmers are often constrained to friends and family for mental health support, while professional face-to-face therapeutic treatments are rarely obtained [5]. Thus, alternative ways to deliver treatment might be beneficial for farmers [2].

Existing evidence-based treatments for mental disorders have shown to only reduce the burden of mental health disorders by a third [13]; however, symptoms of mental disorders can be effectively reduced with preventive interventions [14, 15]. As a recent meta-analysis showed, psychological interventions can prevent or delay the onset of Major Depressive Disorder (MDD) by focusing on individuals with increased risk (selective prevention) or with subclinical depressive symptoms (indicated prevention) [16].

### Internet- and tele-based interventions

Easily accessible preventive interventions, as implemented in this study, could increase farmers’ ability to overcome reported challenges. Internet- and mobile-based psychological interventions (IMIs) have been shown to be effective in working participants [17] as well as for preventing MDD onset and treating subthreshold depression in the general population [16, 18–21]. In a similar context, researchers have begun to evaluate online interventions in Australian farmers to reduce stigma surrounding suicide and to combat rural isolation for farmers [22].

Although access to the internet has increased significantly in Germany in recent years, rural areas still face problems using Internet services [23]. Therefore, tele-based coaching is an important addition to existing preventive programmes against depression, especially in rural communities. Evidence also suggests that tele-based coaching, in comparison to treatment-as-usual, is effective in reducing symptoms of depression [24].

Despite its effectiveness, the uptake of health care interventions in routine practice remains low and costly [25, 26]. Only 14% of evidence-based health care interventions are used in routine care [27]. While many studies focus on the implementation of interventions for the treatment of mental disorders, there is little research on the implementation of preventive interventions. The few studies relate to the prevention of eating disorders and depression in adolescents and young adults [28, 29].

### Implementation in rural areas

Technology-based solutions appear to be an increasingly viable option as they have the potential to overcome disparities in access for rural mental health care services [30, 31]. In addition, computerised Cognitive Behavioural Therapy interventions for anxiety and/or depression seem to be acceptable among people living in rural and remote areas [32]. Moreover, barriers and facilitating factors for the implementation of health care interventions in rural areas have been studied: Current evidence suggests that close collaborations with professional institutions, training of employees and perceived credibility of the treatment may facilitate successful interventions [33]. These facilitating factors may be achieved by supporting government agencies, qualified program managers or empirical evidence of efficacy [33]. Furthermore, increased public awareness for mental disorders [34] as well as for the benefits of telehealth [35] might be beneficial.

In addition to the participants, perspectives of all people involved in the implementation and delivery of this treatment should be considered. For example, health care staff in rural areas may prioritise staff attitudes and beliefs towards treatment [36, 37] as well as the leadership and organisational structures of the clinic and the community [37]. Likewise, organisational readiness within rural communities is imperative for the successful implementation of telehealth services [38].

Implementing mental health services in rural areas faces specific difficulties since existing studies disregard the diversity of rural settings, are rarely based on well-developed theories and show methodological weaknesses [39]. Studies exist regarding particular aspects of implementation in rural areas (e.g. acceptance of interventions). However, there is a lack of comprehensive, multi-level implementation research in routine care, especially with regards to the implementation of technology-based interventions for mental disorders in rural areas.

### A nationwide pilot project

This study is part of a national depression prevention program for farmers, gardeners and foresters (“With us in balance”) carried out by the German Social Insurance company for Agriculture, Forestry and Horticulture (SVLFG, www.svlfg.de). The study aims to evaluate the implementation of tailored IMIs and a personalised tele-based coaching as an extension to existing face-to-face group interventions. In addition to the implementation study, it is evaluated in parallel running, randomised controlled trials whether the internet- and tele-based interventions are (cost-)effective in reducing depressive symptoms and other mental health concerns as well as in preventing the onset of clinical depression in this specific target group of farmers, gardeners and foresters [40, 41].^1^

### Evaluation frameworks

Implementation success is considered as a multi-dimensional construct. In this study, the evaluation is based on the Reach, Effectiveness, Adoption, Implementation and Maintenance (RE-AIM) framework [42] as it helps to structure this multifaceted evaluation on individual and organisational levels. The RE-AIM framework is one of the most used evaluation frameworks in the implementation setting and facilitates to assess the quality, speed and impact of implementation efforts. In addition, the use of the Consolidated Framework for Implementation Research (CFIR) enables a deeper understanding of the mentioned ‘implementation’ dimension, as CFIR offers a pragmatic structure for approaching compound and interacting states in the implementation of interventions [43].

Staff are part of a dynamic interaction within the organisation and are a key component to successful implementation. Previous literature showed the importance to examine different levels, when implementing in rural areas, e.g. staff attitudes and beliefs [36, 37], management and organisational structures, and organisational readiness [38]. The following constructs focusing on the involved employees aim to capture different aspects of the implementation process:
Degree of Normalisation: Normalisation refers to activities that people pursue to integrate an innovation into their everyday routine. According to the Normalisation Process Theory, normalisation is defined as the extent to which a new intervention is considered as a normal part of daily work [44].Determinants in the implementation process: The Theoretical Domains Framework (TDF) provides an integrative framework model to identify drivers of behavioural change that could influence determinants in the implementation process [45].Organisational leadership: Minimal attention is given in research to the organisational context, although it may have a significant impact on the implementation of evidence-based practices [46]. Therefore, this study collects information regarding implementation leadership which may have an impact on the program’s ability to drive change and innovation [47].Organisational readiness for change: This construct refers to the extent to which employees of an organisation are willing to implement organisational change, with particular focus on psychological and behavioural aspects [48].

### Research questions

The aim of this study is the multi-level evaluation of the implementation success and stepwise nationwide rollout of the following new preventive services: a) GET.ON online health trainings with 7 guided IMIs, and b) personalised tele-based coaching provided by external companies in addition to existing on-site group interventions offered by the SVLFG.

Our study seeks to address the following research questions:
How successful is the implementation of internet- and tele-based interventions in terms of reach, effectiveness, adaptation, implementation and maintenance on an individual (participants, staff) and organisational level?How effective is the implementation in terms of intervention uptake, normalisation into everyday life, and implementation costs?What are the experiences and impressions of the participants receiving internet and tele-based interventions? In particular, to what degree do participants report: a) acceptance and use of the technology-based treatment, b) satisfaction with the intervention considering their expectations, and c) perceived barriers and facilitators to use the intervention?Which barriers and facilitating factors can be identified for advising on prevention services at staff level?What determinants for implementation success in rural areas can be identified by focusing on employees involved in the referral process?Which similarities and differences can be identified between internet- and tele-based interventions with regards to implementation success and other determinants metrics of implementation effectiveness?

## Methods

### Design of the study

This study is a prospective, longitudinal implementation study and is described according to the Standards for Reporting Implementation Studies (StaRI) checklist [49], see Supplementary material. A mixed-methods approach using qualitative interviews, focus groups, quantitative surveys and reporting data is utilised for a comprehensive understanding of the implementation process. The evaluation is based on the RE-AIM framework [42] and the CFIR [43].

The implementation follows a stepwise, nationwide rollout plan which determines the availability of the internet- and tele-based interventions and the enrolment of the insured persons in each rollout region. Each region (2–7 federal states of Germany) undergoes these implementation phases at different times, starting with a pilot implementation phase in Bavaria and Schleswig-Holstein for 1.5 years and following with three rollouts (A, B and C) over 2 years. The initial pilot implementation phase was extended for various reasons (e.g. additional time needed to implement internal structures at SVLFG such as the referral process and documentation of consultations with insurers, additional time to conduct trainings, and unforeseen delayed availability of the tele-based coaching). Based on the Conceptual Model of Implementation Phases [50], the study can be divided into the following phases: exploration, preparation, implementation (6–12 months) and maintenance (12–24 months). The duration of the phases was defined in accordance to the RE-AIM framework that recommends 6 to 12 months for the implementation phase and at least 2 years for the maintenance phase [42]. In addition, the enrolment plan of the SVLFG stipulates that the rollout area is expanded every 6 months and focuses on implementation in this region within these 6 months Fig. 1.

**Fig. 1 Fig1:**
[figure not shown]
Project timeline depicting the Conceptual Model of Implementation Phases [50] including exploration (E), preparation (P), active implementation (I) and sustainment (S) adapted to the stepwise rollout plan

### Enrolment

The insured individuals are advised on the preventive services by approximately 350 employed field workers and in-house staff of SVLFG during their consultations via phone or on-site. In addition, the prevention services are advertised widely through PR activities of the SVLFG (e.g. newspaper articles, radio reports, SVLFG member magazine, lectures and information events) in the federal states where the interventions have been implemented. Interested individuals receive detailed information regarding the offered prevention services and their eligibility at the SVLFG central call centre. Eligible insured persons can choose whether they prefer single (e.g. internet- or tele-based interventions) or group preventive services. The group interventions are delivered on-site and include various topics on mental health issues for this target group (e.g. dealing with stress, handing over the business to the next generation). The registration process is conducted by SVLFG.

Data collection starts with rollout A in April 2019 and is expected to be finished at the project end (April 2021).

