	- Usage of the intervention (e.g. adherence, duration and frequency of contacts)	GET.ON Institute / IVPNetworks	Reportings	Continuous
	- Credibility (Credibility Expectancy Questionnaire) and perceived (dis-)advantages	SVLFG staff- participants	Online-assessment	R0 / R1 / R2 / R3^b^
	- Costs for the intervention	SVLFG	Reportings	Every 3 months
	*Outer Setting:*			
	Acceptance, relevance, utility	Insured person GET.ON Institute / IVPNetworks	Online-assessment Interviews Reportings (e.g. adherence)	T1^a^, T1^a^ Continuous
	*Inner Setting:*			
	- Leadership support (Implementation Leadership Scale)	SVLFG staff-participants	Online-assessment	R0 / R1^b^
	- Organisational willingness to change (Organisational Readiness for Implementing Change questionnaire)	SVLFG staff-participants, implementation team	Online-assessment	R0 / R1 / R2 / R3^b^
	*Characteristics of individuals:*			
	- Degree of normalisation (NoMAD)	SVLFG staff-participants	Online-assessment	R0 / R1 / R2 / R3^b^
	- Determinants of Behavioural Change (Discriminant Content Validation of the TDF Questionnaire)	SVLFG staff-participants)	Online-assessment	R1^b^
	- Barriers and facilitating factors at the consultations	SVLFG staff-participants	Focus groups	11/2017–02/2019
	*Process:*			
	- Evaluation of the implementation process (e.g. implementation activities, barriers and facilitating factors)	Implementation team	Interview	Every 6 months
	- Dissemination activities	SVLFG	Reportings	Every 3 months
	- Usage by employees	SVLFG staff-participants	Reportings	Every 3 months
	- Implementation costs	SVLFG	Reportings	Every 3 months
**MAINTENANCE (individual + organisatonal level)**	Sustainability of interventions (effectiveness)	Insured	Online-Assessment	T2^a^
	Referrals back to SVLFG and use of further offers	GET.ON Institute / IVPNetworks / SVLFG	Reportings	Continous
	Evaluation of the current implementation and further use of the technologies	SVLFG staff-participants	Online-assessment	R3^b^
	Sustainability of implementation (referral and uptake rates)	GET.ON Institute / IVPNetworks / SVLFG	Reportings	R3^b^

Notes

^a^time of insured-assessment depends on the date of intervention start

^b^time of employee-assessment depends on the date of the rollout in the specific area

*Abbreviation*: *m* month

Assessments: T0 (pre intervention), T1 (3 months after starting the internet-based training / 6 months after starting the tele-based intervention), T2 (12 months after starting the intervention)

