Rollout: R0 (rollout start), R1 (6 months after rollout), R2 (12 months after rollout), R3 (18 months after rollout)

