### Trial status

Recruitment has been started in April 2019. Participants will be continuously included until the end of the study. Data collection is ongoing.

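### On the protocol's own dates, R3 for rollout C and T2 for anyone starting after April 2020 fall after data collection ends

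*Protocol article*

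**What the plan says.** The Enrolment section gives the only calendar for data collection: "Data collection starts with rollout A in April 2019 and is expected to be finished at the project end (April 2021". The abstract agrees on the length: "data collection will occur at baseline and continuously across 24 months".

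The Design section describes a pilot phase, "following with three rollouts (A, B and C) over 2 years", and adds that "the rollout area is expanded every 6 months". It plans 6 to 12 months of implementation and 12 to 24 months of maintenance. It presents these lengths as consistent with a RE-AIM recommendation of "at least 2 years for the maintenance phase".

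The notes to Table 1 count staff time points from the rollout date of the area concerned, ending with "R3 (18 months after rollout". They count participant time points from the intervention start: T1 at 3 months (internet) or 6 months (telephone), and "T2 (12 months after starting the intervention".

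Trial status sets no earlier cut-off for entry: "Participants will be continuously included until the end of the study".

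Table 1 puts the sustained effect on participants at T2, and the sustained referral and uptake rates and the staff evaluation at R3. The Maintenance section puts the concluding staff survey at the end of the project.

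**The concern.** A fixed end date, staggered regional starts and entry up to the last day cannot all coexist with a follow-up of 12 months per participant and 18 months per region. Some planned assessments fall outside the window by construction, and they are not a random subset: they belong to the last region and to late entrants everywhere.

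T2 and R3 carry the long-term participant outcomes and the sustained-implementation measures, so those results will rest on earlier regions and earlier entrants. T1 is also affected unequally. The telephone service has the later T1, so more of its entrants run out of calendar time, in a study that sets out to compare the two services. Unless forms that could never fall due are separated from forms that were due and not returned, response rates will mix the two.

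**Working it through.** **Inputs.** Month 0 is April 2019 and month 24 is April 2021 (Enrolment), which reproduces the 24 months in the abstract. Three rollouts 6 months apart (Design of the study) start at months 0, 6 and 12: April 2019, October 2019 and April 2020. The dates of B and C are derived from this rule, because Fig. 1 is not shown. Assessment lags come from the notes to Table 1.

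**Staff time points.** The date of Rk is the area's start + 6k months, and it must be no later than month 24.

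| Rollout | Start | R1 | R2 | R3 | R3 in window? |
|---|---|---|---|---|---|
| A | Apr 2019 | Oct 2019 | Apr 2020 | Oct 2020 | yes |
| B | Oct 2019 | Apr 2020 | Oct 2020 | Apr 2021 | on the end date |
| C | Apr 2020 | Oct 2020 | Apr 2021 (on the end date) | Oct 2021 | no, 6 months late |

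**Last participant start that still allows each assessment.** Latest start = 24 − lag.

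- T2: 24 − 12 = month 12, April 2020.
- T1 telephone: 24 − 6 = month 18, October 2020.
- T1 internet: 24 − 3 = month 21, January 2021.

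These cut-offs depend only on the end date, not on the rollout spacing. Rollout C opens in month 12, so 0 of its 12 entry months allow T2. T1 remains possible for 9 of 12 entry months (internet) and 6 of 12 (telephone).

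**Share of entrants who can reach each assessment (illustration).** The documents give no accrual curve, so two assumptions are shown. Under uniform total accrual the share is (24 − lag)/24. Under equal constant accrual per open region it is the sum of max(0, 24 − start − lag) over regions, divided by the sum of (24 − start) = 24 + 18 + 12 = 54 region-months.

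| Assessment | Uniform | Equal per open region |
|---|---|---|
| T2 | 12/24 = 50% | (12 + 6 + 0)/54 = 33% |
| T1 telephone | 18/24 = 75% | (18 + 12 + 6)/54 = 67% |
| T1 internet | 21/24 = 87.5% | (21 + 15 + 9)/54 = 83% |

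Of the 500 to 800 participants expected in the section on insured persons, about 167 (500 × 18/54) to 400 (800 × 0.50) could reach T2 before any dropout. The internet-minus-telephone gap in reachable T1 is 87.5 − 75 = 12.5 percentage points, or 83.3 − 66.7 = 16.7.

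**Sensitivity to rollout spacing s.** R3 for C needs 2s + 18 ≤ 24, so s ≤ 3 months against the stated 6. Under equal accrual per open region, the share unable to reach T2 is 57% at s = 3, 60% at s = 4, and 67% at s = 6 and s = 8.

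**Phase lengths.** The shortest planned implementation plus maintenance is 6 + 12 = 18 months; rollout C has 24 − 12 = 12. Even rollout A, after the minimum 6 months of implementation, has 24 − 6 = 18 months left, short of 2 years.

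**Concluding staff survey.** R3 (Table 1) falls in October 2020, April 2021 and October 2021 for A, B and C. The project end (Maintenance section) is April 2021. The two coincide only for B.

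**The case against.** The strongest reply is that this is ordinary administrative censoring in an uncapped routine-care study. Its analyses are largely descriptive. It defines implementation success by uptake, normalisation and efficiency, and parallel randomised trials address efficacy. Analysis sets are often left to the full protocol or SAP, the end date is only an expected one, and the timeline figure is not shown.

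Much of this stands, and it limits how far the point goes. A reader might infer four stronger things that the documents do not support:

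- *That maintenance cannot be observed at all in rollout C.* Referrals back and use of further offers are reported continuously, uptake is monitored in each region's maintenance phase, NoMAD is also due at R2, and the text places the concluding survey at project end. NoMAD at R2 has no slack in C, and it falls within maintenance only if implementation there takes less than the full 12 months.
- *That unreachable forms will be counted as dropout.* Non-completion is defined by modules, call minutes, 8 weeks of inactivity or interruption, not by survey return. The analysis text says only that missing-data patterns will be analysed and corrected. It does not say how assessments that never fell due are treated.
- *That R3 and T2 results will be presented as nationwide.* No passage says so, and the quantitative analysis plans comparisons across rollout areas at different phases.
- *That 33% and 50% are bounds.* They are two accrual scenarios. Regions span 2 to 7 federal states, and equal regional accrual is an assumption. Whether the pilot states contribute data is not stated either.

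The reply does not remove the conflict between stated facts. Follow-up after April 2021 would contradict the Enrolment section, and an earlier entry cut-off would contradict Trial status.

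**Conclusion.** The point holds in a limited form. R3 for rollout C falls six months after the stated end of data collection, and R3 for B and R2 for C have no slack. T2 is out of reach for every start after April 2020, so essentially for all of rollout C. T1 is out of reach for internet starts after January 2021 and telephone starts after October 2020. Rollout C therefore loses T2 and the R3 time point, and keeps the other maintenance measures named above.

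The participant cut-offs rest only on the stated end date and the lags in Table 1. The R3 result also rests on the 6-month spacing. The shares of entrants depend on assumed accrual and serve only to show that the T2 loss is not marginal. Two smaller inconsistencies need no accrual assumption: the phase lengths do not accord with 2 years of maintenance in any of rollouts A to C within this window, and the concluding survey has two dates that agree only for B.

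**What to change.** Before the data cut:

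1. Define the T2 set as entrants by April 2020, and the T1 sets as internet entrants by January 2021 and telephone entrants by October 2020. Use these as the denominators for response and attrition. Treat later entrants as administratively censored for the assessment concerned, while still counting them for reach.
2. State that R3 conclusions apply to rollouts A and B, that T2 conclusions apply to entrants by April 2020, and that C is reported to R2.
3. Optionally, keep the online surveys open after April 2021. R3 for C needs them until October 2021. T2 for the last entrants needs them until about April 2022 if inclusion runs to April 2021.
4. Correct the statement that the phase lengths accord with at least 2 years of maintenance, noting that rollout C has 12 months in total.
5. Give the concluding staff survey a single date, either R3 or project end, in both Table 1 and the Maintenance section.

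The cost is protocol wording and analysis-set definitions, plus survey running time if item 3 is taken up. The downside is a narrower maintenance conclusion.
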